### Method of implementing the randomisation/allocation sequence

Allocation will be performed using a validated web-based system (Sealed Envelope Ltd). A letter will be sent to the participant’s GP, notifying them of their patient’s participation in the study and confirming randomisation assignment.

Carers will be randomised as a dyad with the person with MLTCs and frailty. Each participant will be given a unique participant identification (ID) number at randomisation. For people undertaking the intervention with a carer, these ID numbers will be linked.  Participant ID numbers will be used to identify the individual participant throughout the study and will not be re-assigned to any other participant. Due to the nature of the intervention, blinding of the participants and the study team to allocation is not possible. The allocation will be documented within the trial master file and, where possible, participant medical notes.

## Blinding

It is not possible to blind participants and intervention providers to allocation, due to the nature of the intervention. Furthermore, outcome assessors will not be blinded as this feasibility study does not aim to evaluate intervention effectiveness. Scripts for helping participants who need support to complete PROMs will be developed to minimise response bias.

## Trial intervention

PERSONAL-AGILITY is a complex intervention that uses a range of approaches tailored to individual needs. This study will have the option to use different technology that can be used at home and in the community to help adapt to individual needs and preferences.

### Technology

The PERSONAL AGILITY intervention will use novel technology where it reduces burden and adds value for the individual, including bespoke interactive digital platforms and wearable technology (e.g., physical activity monitors, such as Fitbits or apple watches), to support:

- Collection and review of clinical information; by both participants and health and care professional (HCPs) involved in the delivery of PERSONAL AGILITY
- Intervention delivery; some areas may use existing services
- Ongoing monitoring/support; including provision of feedback, reminders/alerts, virtual consultations and peer support.

Importantly, the use of technology will complement, not replace, face-to-face contact. Many individuals may prefer the personal nature of face-to-face discussions with their HCPs and personal contact may facilitate conversations that would not be had via purely digital means. A solely digital approach may not be inclusive for all individuals, so alternative non-digital means of engagement will be available where appropriate/preferred. PERSONAL AGILITY technology will involve the following key platforms, which we have specifically refined to meet the needs of people living with MLTCs and frailty, and those who care for them:

#### MyHealthMapp

MyHealthMapp is a tool designed to facilitate a conversation around the 24-hour physical behaviours between people living with long-term conditions and their health care professional. MyHealthMapp is an online tool (web application) designed to track/log health, wellbeing and 24-hour physical behaviour data (trend of data, changes, patterns of activity) automatically via a physical activity device and/or entered manually. MyHealthMapp compares the data to personalised population norm values and generates a RAG (red, amber, green) rating to help users and their HCPs understand and interpret their results. MyHealthMapp also hosts short information videos for all measurements on the platform to help people understand what the physical activity and health variables mean. MyHealthMapp generates personalised targets for certain variables, i.e., step targets, based on participants previous results. Data stored on MyHealthMapp includes:

- daily stepping
- fitness
- non-stepping activity
- physical function
- strength
- sitting and sleep.
- glucose levels
- body weight
- wellbeing and holistic health.

#### Steps4Health

Steps4Health is a physical activity web application targeting 24-hour physical behaviours for people wanting to become active or living with a long-term condition. Steps4Health provides a personalised physical activity programme and ongoing support to help improve users’ health by becoming more active (focused on stepping, sweating [moderate to vigorous intensity physical activity] and strengthening) whilst also promoting improved sleep and reduce sitting timeSteps4Health includes:

- A personalised physical activity programme tailored to the user’s fitness and mobility level
- A walking programme to help the user increase their steps gradually for health benefits
- Online exercise sessions catered to all abilities, from seated workouts to full-body exercises. These sessions are available on demand for use at a time that suits the user
- Daily activity trackers including walking, sitting, workouts, and sleep
- Daily activity goals and notifications
- Direct access to the physical activity experts at the Leicester Diabetes Centre
- Competitions, challenges, and award notifications
- Interactive content about getting and staying active
- A chat forum offering vital peer support

#### Personalised videos

Videos, populated with data personalised to each participant and clinically approved health information, will be used to provide participants with a short summary of their current health and physical activity data, with a brief description of what the data means, before their intervention appointments. These videos will be used to help people:

- To break down complex terminology and enable them to understand their own results.
- Re-watch/ pause the video to help them process the information or write anything down.
- Show the video to others (i.e. family and/or carers)^84, 85, 86, 87^.
- Consider what they would like to speak about and any questions they may have ^84, 85, 86, 87^.

The aim of personalised videos are to improve the quality and experience of clinical appointments by generating informed discussions and allowing more time for participant questions and planning of goals/next steps ^84, 85, 86, 87^. Together with MyHealthMapp, personalised videos will facilitate shared decision making (see section 6.8) between the person and their HCP and enable them to be more active in their own care.

## Delivery of care

The PERSONAL-AGILITY intervention will be delivered by the research team and HCPs trained to deliver the PERSONAL-AGILITY intervention, using a range of delivery methods (in person, phone, online). The focus of the intervention (improvement of sleep, physical activity and reduction of sedentary behaviour) will be guided by a holistic assessment, facilitated by MyHealthMapp, using a shared decision-making (SDM) approach.

Shared decision making is a collaborative process in which the person and health care provider work together to make healthcare decisions that are best for their needs and circumstances^88^. Each decision will take into account the HCP knowledge/ experience and evidence around the treatment options as well as the participant’s preferences and values^88^. The SDM intervention will follow the 5 steps to SDM from the “SHARED approach” as outlined below ^88^:

- Seek the participant’s participation
- Help the participant explore and compare treatment options
- Assess the participant’s values and preferences
- Reach a decision with the participant
- Evaluate the participants decision

To help facilitate the SDM process the HCP will create a safe environment to support the conversation and utilise tools to facilitate the conversation (e.g., personalised goal setting) and may include the use of personal decision-aids and other documents designed to support participant engagement.

Linking participants with community groups within their locality will also be a feature of the intervention (this may not be available to all participants), and where possible, they will be supported to access activities groups and services in their community that either directly or indirectly reduce their sedentary behaviour and increase physical activity. ‘Direct’ refers to groups which focus on increasing physical activity e.g., a seated exercise class. ‘Indirect’ refers to groups which have a non-physical activity focus but increase participation and may increase physical activity through the functional activity needed to prepare for going to the group, travelling to the group, and movement during the group.

## Usual care

Ongoing standard care (for participants in the control group) will continue to be delivered by participants’ usual NHS service providers in primary and secondary care and will not be altered or standardised as part of the trial. Usual care will reflect routine practice where participants may be referred into single disease rehabilitation. Attendance at any rehabilitation programme (or similar) will be recorded. Participants in the control group will receive generic information on the 24-hour physical behaviours.

# Trial assessments

## Trial visit schedule

Trial procedures and study outcomes related to the trial will be distinct from measures undertaken as part of the PERSONAL-AGILITY intervention. Trial assessments measured at research visits will be used to examine the feasibility and acceptability of the PERSONAL-AGILITY intervention on the outcomes outlined in sections 7.1.1 and 7.1.2.

Visits will occur at weeks 0, 12 and 24. As per baseline assessments, it is intended that all assessments at each follow-up time point will be completed on a single day but may occur across multiple visits provided they are completed with a maximum 14-day window. At each time point, willingness to continue will be confirmed and documented on the CRF, and participants will be asked to undertake all the measures outlined. Relevant assessments will be performed at each visit as described. There will also be an option for home and community-based testing in line with PPI suggestions to help make the intervention more inclusive where possible.

An unscheduled visit can be used when a participant misses their appointment, is outside of their visit window due to unforeseen circumstances, or repeat assessments are required, but this will be logged accordingly as being outside of intended trial timelines and/or additional assessments (e.g., protocol deviation).

### Feasibility of trial methodology

The following measures will be examined to determine the feasibility of a future RCT of the PERSONAL-AGILITY intervention:

**Eligibility rate**

- Eligibility rates
- Reasons for ineligibility

**Recruitment rate**

- Recruitment rates
- Recruitment rates amongst people from minority ethnic and socioeconomically deprived backgrounds
- Basic characteristics (age, sex, ethnicity, frailty status if known) of those who decline
- Reasons for declining

**Retention**

- Rates of attrition at each stage of the study (screening, consent, randomisation, baseline, follow up (12 and 24 weeks)
- Reasons for withdrawal

**Trial outcome measures**

- Outcome measure completion rates for all secondary measures

Time taken to complete outcome measures

- Reasons for missing data (if known)

**Other feasibility measures**

The feasibility of having a co-primary outcome specifically for carers in the definitive trial will be explored using data based on rates of recruitment of carers, carer completion rates and their feedback gathered as part of the process evaluation/ assessment of acceptability.

Quantitative feasibility data will be gathered from a range of sources, including screening and recruitment logs and CRFs.

### Acceptability of trial methodology and intervention

The acceptability of the trial and intervention will be measured both quantitatively and qualitatively. This section outlines the components of acceptability that will arise directly from trial and intervention data. Section 7.3 provides further information about qualitative acceptability data. This will be complemented and expanded by additional data from a mixed methods process evaluation data, which is discussed in detail in section 7.3.

Quantitative data relating to acceptability includes:

- Rates of uptake and engagement with each component of the PERSONAL-AGILITY intervention, including but not limited to:
  - MyHealthMapp
  - Steps4Health
  - Linking to community services and groups
  - Attendance at community services and groups

These data will be gathered from reports from the digital tools, trial documents and a data capture form which will be completed by the physical activity officer (A draft example is provided in appendix B).

- Rates of adherence to the intervention

Intervention adherence will be captured using a bespoke diary, including:

- Frequency, duration, intensity, time, type and consistency of physical activity
- Bouts of non-sedentary time
- Reasons for non-adherence

The above two measures will provide an indication of participants engagement with the intervention received ^89^.

- The 24-hour Physical Behaviour Burden Questionnaire

At weeks 12 and 24, the 24-hour physical behaviour burden questionnaire will be used to assess burden in participants in the intervention group, as a PROM relating to intervention acceptability. This is a modified from the exercise therapy burden questionnaire to establish burden across all of the 24-hour physical behaviours. The original exercise therapy burden questionnaire is a 10-item instrument that measures intervention burden in participants with long term conditions.^90^ The measure has been modified in the absence of any other appropriate measure of burden.

## Secondary outcomes

The selection of a primary outcome measures for an intervention which:

- Allows for individualisation amongst participants in the intervention group, in line with a SDM approach
- Allows for the focus of the intervention to change within a single individual participant over time, also in line with a SDM approach
- Allows for the inclusion of a carer as an equal participant within the intervention

May present a challenge for the selection of an appropriate, sensitive and responsive primary outcome measure which is also meaningful to this population. We will gather data on a range of objective and patient reported outcomes (PROMS) to establish which measure(s) may be the most appropriate primary measure in a future definitive trial.

The following secondary outcomes will be gathered to inform the selection of a primary outcome measure/ co-primary outcomes for carers and people with MLTCs and frailty. This determination will be made alongside feasibility data relating to outcome measure completion rates. Objective tests will all have standardised standard operating procedures (SOPs) to ensure consistency of measurement. All participant groups (carers and people with MLTCs and frailty) will do all the tests, except where a specific population is identified. PROMS may be completed with the support of researchers (using standardised scripts) or may be completed by the participants at the study appointments, or taken home and returned at a later date.

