### Physical function

- **Short Physical Performance Battery**

At baseline, weeks 12 and 24, the Short Physical Performance Battery (SPPB) will be used to objectively measure physical function. The SPPB measures balance, gait speed and ability to stand from a chair^93^. It comprises three tests outlined below, each scored out of 4 (for a maximum total score of 12) in accordance with available guidance:

- Chair sit-to-stand: The participant will start from a seated position on a hard, upright chair (such as a dining chair) of standardised height, with the feet flat on the floor and the knees bent at 90°. For the test, the time taken for the participant to stand up fully and then return to sitting 5 times without using the hands is measured.
- Standing balance: Static standing balance is tested in three progressive positions. If the participant can maintain the specified position for at least 10 seconds, then the position is progressed to the next stage:
  - Feet together
  - Semi-tandem
  - Tandem
- Gait speed: Gait speed is calculated from the time taken for the participant to walk 4 metres at their usual speed on a level course. It is measured twice with a short break in between, and the best score used.
- **Berg Balance Scale**

At baseline, weeks 12 and 24, the berg balance scale will be used to assess the participants balance^94^. The berg balance scale includes 14 tasks that are scored on a 5 point scale, with 0 as the lowest level of function and 4 as the highest^94^, with the total score being out of 56. The berg balance scale is a valid and reliable to assess balance^95^.

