## Summary of baseline data and flow of participants

A CONSORT diagram, based on the extension to randomised pilot and feasibility trials, showing the flow of participants through the study will be produced^123^. Data will be checked for outliers and missing values and validated using the defined score ranges. Baseline demographics will be summarised by treatment group and for the total population using number (percentage) for categorical variables and mean (standard deviation) for continuous variables (unless they are found to be skewed in which case median and interquartile range will be presented). Clinically meaningful differences between groups at baseline will be described, but no statistical testing will be conducted to compare baseline characteristics by treatment group^124^. The basic baseline characteristics (age, gender, frailty status and ethnicity) of those who participated and declined will be explored where possible.

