## Secondary trial outcome analysis

Outcomes at 12- and 24-weeks follow-up will be summarised by randomised group and overall using mean (SD) and median (IQR) for continuous variables and count (percentage) for categorical variables. The number of SAEs will be presented overall and by randomised group.  All exploratory analyses will be considered hypothesis generating rather than providing firm conclusions and no p values will be reported.

Outcome acceptability will be determined by quantifying the amount of missing data across the secondary outcomes. The proportion of missing data (number, %) will be reported for each outcome, but no imputation will be performed to account for this missing data. Reasons for missing data will be gathered where possible.

Quantitative acceptability data including:

- rates of uptake and engagement with each component of the PERSONAL-AGILITY intervention
- adherence to the intervention (e.g., frequency, intensity, time and type of activity)

will be reported descriptively using number and percentage.

PROMS relating to intervention acceptability (the 9-item shared decision-making questionnaire) will be examined descriptively, by reporting at 12- and 24-weeks follow-up using mean (SD) and median (IQR).

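### The planned outcome summaries contain no within-person change, so they do not supply the responsiveness evidence that choosing a future primary outcome calls for

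*Protocol*

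**What the plan says.** Section 7.2 of the Protocol (Secondary outcomes) gives the reason for the outcome battery: data are gathered "to establish which measure(s) may be the most appropriate primary measure in a future definitive trial", and also to inform possible co-primary outcomes for carers. It describes the "selection of an appropriate, sensitive and responsive primary outcome measure which is also meaningful to this population" as something that may be difficult, given an individualised intervention whose focus can shift. On completion it adds: "This determination will be made alongside feasibility data relating to outcome measure completion rates".

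Section 9.5 (Secondary trial outcome analysis) then states the analysis: "Outcomes at 12- and 24-weeks follow-up will be summarised by randomised group and overall using mean (SD) and median (IQR) for continuous variables", with counts and percentages for categorical variables. It adds that "Outcome acceptability will be determined by quantifying the amount of missing data across the secondary outcomes". It rules out p values and imputation. It names no change from baseline, SD of change, baseline-adjusted difference or correlation.

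For baseline, section 9.2 says: "Baseline demographics will be summarised by treatment group and for the total population". Outcome scores at baseline are not named there or in 9.5.

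The measures themselves are repeated. For example, section 7.2.2 says: "At baseline, weeks 12 and 24, the Short Physical Performance Battery (SPPB) will be used to objectively measure physical function". Table 1 shows the same pattern across the battery, with the Zarit interview for carers only.

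**The concern.** Responsiveness is about whether a measure moves within people, relative to how variable that movement is. It rests on the mean and SD of each person's change, and the SD of change depends on the baseline to follow-up correlation. Separate summaries at week 12 and week 24 contain neither the SD of change nor the correlation. Without baseline outcome scores they do not give the mean change from baseline either.

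So the section that states the purpose and the section that states the analysis do not meet. Frail participants and their carers complete about a dozen measures three times, largely so that one can be chosen for the next trial. The stated output leaves out the descriptive figures that bear most directly on one of the named properties. The same correlation would also help to size a baseline-adjusted definitive trial. Sizing is not a listed objective in section 2, but section 9.7 includes optimising the definitive trial design among its aims.

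**Working it through.** The plan states no figure to reproduce: section 9.1 takes n=50 from a range of 24 to 50 in the literature, without a formula. The check is therefore what the stated summaries can and cannot determine.

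**Inputs from the Protocol.** n=50 people with MLTCs and frailty (9.1); 2:1 allocation (section 3), about 33:17; the green retention threshold of 70% at 24 weeks (Table 5), so 0.70 × 50 = 35, about 23:12; carer recruitment thresholds of 20% and 50% (Table 5), so 10 to 25 carers.

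**Assumptions, not in the Protocol.** Mean change of 0.3 SD, equal SDs at both visits, and a baseline to follow-up correlation r between 0.3 and 0.9.

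**1. Do visit means and SDs determine responsiveness?** SD of change = SD × √(2(1 − r)), and standardised response mean (SRM) = mean change / SD of change.

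| r | SD of change (in SDs) | SRM | 1 − r² |
|---|---|---|---|
| 0.3 | 1.18 | 0.25 | 0.91 |
| 0.5 | 1.00 | 0.30 | 0.75 |
| 0.7 | 0.77 | 0.39 | 0.51 |
| 0.9 | 0.45 | 0.67 | 0.19 |

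Every row has the same visit means and SDs. The variance factor for a baseline-adjusted comparison, 1 − r², differs by 0.91 / 0.19 = 4.8 between the extremes of the assumed range.

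**2. What do the stated summaries give?** They give a crude between-arm difference at follow-up, in SD units. Its 95% half-width is t × √(1/n₁ + 1/n₂):
- 33:17: 2.011 × √(1/33 + 1/17) = 0.60 SD
- 23:12: 2.035 × √(1/23 + 1/12) = 0.73 SD, rounded up from 0.725

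With baseline adjustment at r=0.7, multiply by √0.51 = 0.714, giving about 0.43 and 0.52 SD.

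**3. How precise would change statistics be?** The approximate 95% half-width of the SRM is t/√n:
- n=50: 2.010/√50 = 0.28
- n=35: 2.032/√35 = 0.34
- by arm at 23 and 12: 2.074/√23 = 0.43 and 2.201/√12 = 0.64
- carers, both arms together, before any loss, at 25 and 10: 2.064/√25 = 0.41 and 2.262/√10 = 0.72

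**The case against.** The strongest reply is that this is detail for a statistical analysis plan. Change scores and correlations are routine derived outputs, section 9.5 does not forbid them, and the paired data will exist. That stands as far as it goes: nothing in the design prevents the table. But 9.5 is not silent. It names the summaries, and those named serve the purpose in 7.2 less well than a simple alternative from the same data.

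Several stronger readings are tempting, and the Protocol does not support them.

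- A reader might infer that responsiveness cannot be used at all. Paired data are collected, the Goal Attainment Scale T-score (7.2.4) carries achievement within it, and mean change can be obtained from visit means on the same people if baseline scores are summarised. What separate summaries lose even then is the SD of change and the correlation.
- A reader might infer that the choice falls to completion rates. Section 7.2 uses completion alongside other data. The topic guides in Appendices D and E ask which outcomes mattered or seemed irrelevant, and section 9.7 integrates the two strands. The missing-data rule in 9.5 concerns acceptability of the measures and is not a selection rule.
- A reader might infer that only completion puts unlike scales on a common footing. Means and SDs by arm allow a crude standardised difference for any continuous scale, which bears on sensitivity to the intervention.
- A reader might take responsiveness as a formal requirement. Section 7.2 names it as a desired property within a described difficulty.

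Precision is also a fair objection. SRMs of 0.25 and 0.39 would hardly be separated at these sizes, and unblinded assessment (6.7) could inflate observed change.

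**Conclusion.** The point holds as a mismatch between sections 7.2 and 9.5 that can be closed at almost no cost. The stated analysis does not supply within-person change, its SD or the baseline to follow-up correlation. The other evidence does not fill the gap: interviews cover the intervention group only (7.3.1) and address meaningfulness, the Goal Attainment Scale is one candidate among many, and the crude follow-up contrast has a half-width of about 0.60 to 0.73 SD.

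The SRM range of 0.25 to 0.67 and the 4.8-fold ratio illustrate what the stated output cannot distinguish. They rest on an assumed 0.3 SD change and assumed correlations of 0.3 to 0.9, with the 4.8 comparing the ends of that range. They are not properties of this trial. The conclusion does not depend on those values. It rests on the wording of 7.2, 9.2 and 9.5, and it does not put the feasibility outcomes in doubt.

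**What to change.** In section 9.5 add, for each candidate outcome at 12 and 24 weeks, separately for people with MLTCs and frailty and for carers, and descriptively without p values:

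- a summary of the baseline score;
- the mean and SD of change from baseline by arm, with a 95% CI for the mean change;
- the baseline to follow-up correlation with a 95% CI.

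In section 7.2 add a sentence saying that these figures will be considered together with completion rates and the interview findings on meaningfulness when the primary outcome, or a carer co-primary, is proposed.

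The cost is a few lines of text and one extra table from data already collected. The downside is imprecision: SRM half-widths of about 0.28 at n=50 and 0.34 at n=35, wider by arm and for carers. The text should say that the figures are indicative and will not be used to rank the measures strictly.
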